# Thrombelastographic haemostatic status and antiplatelet therapy after coronary artery bypass surgery (TEG-CABG trial): assessing and monitoring the antithrombotic effect of clopidogrel and aspirin versus aspirin alone in hypercoagulable patients: study protocol for a randomized controlled trial

**DOI:** 10.1186/1745-6215-13-48

**Published:** 2012-04-27

**Keywords:** Coronary artery bypass, CABG, Thrombelastography, TEG, Multiplate aggregometry, Graft patency, Thromboembolic, Antiplatelet, Clopidogrel, Aspirin

## Abstract

**Background:**

Hypercoagulability, assessed by the thrombelastography (TEG) assay, has in several observational studies been associated with an increased risk of post-procedural thromboembolic complications. We hypothesize that intensified antiplatelet therapy with clopidogrel and aspirin, as compared to aspirin alone, will improve saphenous vein graft patency in preoperatively TEG-Hypercoagulable coronary artery bypass surgery (CABG) patients and reduce their risk for thromboembolic complications and death postoperatively.

**Methods/Design:**

This is a prospective randomized clinical trial, with an open-label design with blinded evaluation of graft patency. TEG-Hypercoagulability is defined as a TEG maximum amplitude above 69 mm. Two hundred and fifty TEG-Hypercoagulable patients will be randomized to either an interventional group receiving clopidogrel 75 mg daily for three months (after initial oral bolus of 300 mg) together with aspirin 75 mg or a control group receiving aspirin 75 mg daily alone. Monitoring of antiplatelet efficacy and on-treatment platelet reactivity to clopidogrel and aspirin will be conducted with Multiplate aggregometry. Graft patency will be assessed with Multislice computed tomography (MSCT) at three months after surgery.

**Conclusions:**

The present trial is the first randomized clinical trial to evaluate whether TEG-Hypercoagulable CABG patients will benefit from intensified antiplatelet therapy after surgery. Monitoring of platelet inhibition from instituted antithrombotic therapy will elucidate platelet resistance patterns after CABG surgery. The results could be helpful in redefining how clinicians can evaluate patients preoperatively for their postoperative thromboembolic risk and tailor individualized postoperative antiplatelet therapy.

**Trial registration:**

Clinicaltrials.gov Identifier NCT01046942

## Background

Coronary artery bypass surgery (CABG) is conducted in approximately one million patients a year worldwide. The success of the operation is highly dependent on the vascular bypass remaining open. Saphenous vein graft (SVG) is the most commonly used bypass conduit
[1]. SVG occlusion is reported from 5% to 15% within the first year
[1,2]. Thrombosis of the SVG is the primary reason for occlusion in the first days and weeks after surgery; hereafter the processes of intimal hyperplasi and progressive graft atheroschlerosis are assumed to gradually play a greater role in graft occlusion
[3,4].

### Hypercoagulability and thromboembolic risk

Recent observational studies have shown an association between hypercoagulability measured by thrombelastography (TEG) defined by increased thrombin-induced platelet-fibrin clot strength (TEG-Hypercoagulable) and postoperative/post-interventional thromboembolic complications. Gurbel and colleagues reported that in patients undergoing percutaneous coronary intervention (PCI), 60% of TEG-Hypercoagulable patients developed an ischemic event post-intervention, while this only was the case in 9% of TEG-Normocoagulable patients, *P* <0.0001
[5]. Another observational study in patients undergoing major non-cardiac surgery found that 8 out of 95 (8.4%) of TEG-Hypercoagulable patients had a postoperative thromboembolic complication, while only 2 out of 145 (1.4%) TEG-Normocoagulable patients experienced thromboembolic episodes, *P* = 0.016
[6]. Also, in critically ill patients in the surgical intensive care unit, TEG-Hypercoagulable status has been demonstrated to yield a significantly greater risk for thromboembolic complications
[7]. Our group has conducted a prospective observational study of 200 consecutive CABG patients, and found that TEG-hypercoagulability (defined as TEG maximum amplitude (MA) above 69 mm) was prevalent in 87 patients (43.5%) before surgery, and preoperative TEG-Hypercoagulable patients had a higher risk of a combined endpoint of myocardial infarction (MI), stroke and death after 30 days, as compared to TEG-Normocoagulable patients, 17.2% vs. 6.6%, *P* = 0.019
[8].

Based on the above findings it could be speculated whether TEG-Hypercoagulable patients may benefit from intensified antiplatelet therapy to reduce thromboembolic risk after surgery/intervention.

Furthermore, it has been demonstrated that surgery itself induces hypercoagulability, both after CABG and major non-cardiac surgery
[6,9]. Our study will help elucidate if the extent of this increase in patients who are already TEG-hypercoagulable preoperatively, is an independent risk factor.

### Antiplatelet therapy after CABG

Antiplatelet therapy with aspirin is well established after CABG. Graft occlusion rates in the 1980s were reduced from 20 to 30% in the first year after surgery to 10 to 15%, if aspirin therapy was restarted 6 to 24 hours after surgery
[3]. Clopidogrel is a thienopyridine antiplatelet agent that inhibits adenosine diphosphate (ADP)-receptors on the platelet surface (P2Y12 receptors), thereby reducing platelet activation and aggregation
[10]. Dual antiplatelet therapy with clopidogrel in addition to aspirin is well established in the treatment of acute coronary syndromes and in PCI patients, and has been shown to significantly reduce cardiovascular events and death as compared to aspirin treatment alone in these patients
[10-12]. However, these studies have also reported that dual antiplatelet therapy significantly increases bleeding risk
[10-12].

The role of dual antiplatelet therapy after CABG is still not clear. Current guidelines from the European Society of Cardiology (ECS) and European Association of CardioThoracic Surgeons (EACTS) recommend dual antiplatelet therapy in acute coronary syndrome patients after CABG
[13]. These recommendations are primarily based on the “Clopidogrel in Unstable angina to prevent Recurrent ischemic Events” (CURE) and “Clopidogrel Versus Aspirin in Patients at Risk of Ischemic Events” (CAPRIE) trials
[12,14]. It should be noted though, that the subgroup study of the CURE trial failed to demonstrate any beneficial effect of clopidogrel after CABG
[14]. Furthermore, the CAPRIE investigators performed a subgroup analysis of patients who have had prior cardiac surgery, but did not stratify for different types of procedures (valve surgery, CABG and so on) and also did not take time from surgery to inclusion in the study (up to years) into consideration
[12]. Consequently, these data do not support the routine use of clopidogrel in addition to aspirin after CABG in patients with acute coronary syndrome undergoing surgical revascularization, and this has been corroborated by a recent Cochrane review
[15].

No randomized trial to date has examined the role of clopidogrel after cardiac surgery in acute coronary syndrome patients. The randomized trials have focused on the CABG patient population as a whole. Last year the long awaited “Clopidogrel After Surgery for Coronary Artery Disease” (CASCADE) trial was published. The primary endpoint focused on potentially reduced SVG intimal hyperplasi in patients on dual antiplatelet therapy (clopidogrel and aspirin) as compared to aspirin and placebo therapy. As a secondary endpoint, SVG patency was also examined. The study did not demonstrate significant differences among antiplatelet regimens
[16]. “The Preoperative Aspirin and Postoperative Antiplatelets in Coronary Artery Bypass Grafting” (PAPA-CABG) trialists have published pilot data from the first 100 patients randomized to clopidogrel and aspirin vs. aspirin alone, reporting no difference in SVG patency at 30 days measured by cardiac computed tomography
[17]. Gurbuz and associates have published data from 591 consecutive off-pump coronary artery bypass surgery procedures performed by one surgeon. There was no randomization but historical controls. They demonstrated a significant positive clinical effect of dual antiplatelet therapy on the endpoints of postoperative MI and death
[18]. Gao and colleagues published data from a randomized clinical trial in 2010 showing that SVG patency assessed by multi-slice computed tomography (MSCT) three months after CABG showed significant improvement in SVG patency in patients receiving dual antiplatelet therapy with clopidogrel and aspirin vs. aspirin alone, 92% vs. 86%, *P* = 0.043
[19].

### High on-treatment platelet reactivity and thromboembolic risk

In recent years, there has been a growing acknowledgement of the association between insufficient platelet inhibition from instituted antiplatelet therapy (that is, clopidogrel and/or aspirin) and thromboembolic complications. Studies in PCI patients have demonstrated a significantly higher risk for post-procedure thromboembolic episodes in individuals that demonstrate high on-treatment platelet reactivity to ADP
[3,20-22]. Few studies have demonstrated that after conventional CABG with cardio-pulmonary bypass up to 50% of the patients will be transiently aspirin resistant, and this high on-treatment platelet reactivity has been correlated to early SVG thrombosis after CABG
[3,23]. The platelet reactivity patterns of clopidogrel after cardiopulmonary bypass have not been examined. We will monitor platelet reactivity in our trial to elucidate the patterns and degree of high on-treatment platelet reactivity of aspirin and clopidogrel in the immediate postoperative period and three months after CABG.

### Hypothesis

We have asked the following research questions: Can intensified antiplatelet therapy with the addition of clopidogrel to aspirin as compared to routine aspirin monotherapy significantly improve graft patency at three months in TEG-Hypercoagulable patients? Can dual antiplatelet therapy significantly reduce the heightened risk for thromboembolic complications and cardiovascular death in TEG-Hypercoagulable patients? Does failure of instituted antiplatelet therapy to inhibit platelet aggregation increase patients risk for SVG occlusion and thromboembolic events after CABG?

## Methods/Design

### Study population

Patients over the age of 18 referred to our tertiary institution (Department of Cardio-thoracic Surgery, Rigshospitalet, Copenhagen University Hospital, Denmark) for isolated non-emergent CABG procedure were screened for eligibility. See inclusion/exclusion criteria in Table
1. Patients are enrolled from November 2008 to March 2013.

**Table 1 T1:** Inclusion/exclusion criteria

**Inclusion Criteria**
· Elective/subacute multivessel CABG
· Isolated CABG procedure, no concomittant surgery
· Age >18 years
· Able to give informed consent
**Exclusion Criteria**
· Myocardial infarction >48 h of surgery
· Prior CABG surgery within one month
· Cardiac Shock within 48 h of surgery
· Atrial fibrillation
· Anticoagulation therapy with VKA
· ICH/TCI within 30 days
· Prior peptic ulcer
· Platelet count >150 E9
· Ongoing bleeding
· Known platelet disease
· Allergic to aspirin or clopidogrel
· Liver disease with elevated ALAT/ASAT >1.5x normal
· Creatinine >0.120 mmol/l
· Contrast allergy
· Alcohol or narcotics abuse
· Pregnancy
· Geographically not available for follow-up

This table shows the inclusion and exclusion criteria in the TEG-CABG trial

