### Perioperative anticoagulation

Routinely, aspirin and clopidogrel are discontinued five days before surgery. In patients with acute coronary syndrome 40 mg of Clexane (enoxaparin- a low-molecular-weight heparine (LMWH)) twice daily or 2.5 mg of Arixtra (Fondaparinux) once daily is administered subcutaneously until the day before surgery. After surgery, only off-pump patients received Clexane 40 mg s.c. twice daily until discharged from hospital, all other patients do not receive LMWH after CABG.

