### Thrombelastography (TEG)

Until recently, detection of platelet hyper-reactivity demanded sophisticated and time consuming assays. With the modernization and computerization of the TEG methodology, it has gained more clinical interest in specialities beyond cardiac and liver surgery, in which TEG analysis has been used to guide transfusion regimens since the 1980s
[26]. TEG measures kinetics of clot formation, clot strength, platelet function and fibrinolysis, and thus provides a global picture of the patient’s hemostatic ability and the viscoelastic properties of the clot
[26,27]. The analysis is performed on whole blood, in contrast to routine plasma-based coagulation tests
[26]. For TEG-analysis, whole blood is collected in a 3.2% trisodium citrate vacutainer (Greiner Bio-One, Kremsmünster, Austria) and analyzed within 90 minutes after collection by use of a computerized TEG coagulation analyser (TEG model 5000, Haemoscope Corporation, Niles, IL, USA), but not earlier than 30 minutes after collection.

In the TEG analyser, whole blood is incubated in a heated cup (37°C). Within the cup a torsion wire, which can monitor movement, is suspended. In our series we utilize kaolin as a potent initiator of coagulation other activators of coagulation can be used
[23]. The cup starts rotation, and as fibrin forms between the cup and the pin, the rotation is transmitted from the cup to the pin, and the movement of the pin is registered by a computer and the TEG trace is generated
[26,27]. The TEG trace graphically depicts different stages of the hemostatic process; clotting time, kinetics, strength and lysis (*See Figure
2)
[26,27]. The TEG maximal amplitude (MA) depicts the maximal strength of the clot, and MA values above or equal to 69 mm are diagnosed TEG-Hypercoagulable, according to the manufacturer.

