## Discussion

The evidence for clopidogrel in addition to aspirin after CABG is divergent, although most studies have not been able to demonstrate any beneficial effect of dual antiplatelet therapy. Meanwhile, emerging evidence from observational studies has demonstrated a significantly higher thromboembolic risk in both PCI and CABG patients that are TEG-Hypercoagulable. The TEG-CABG trial is the first randomized trial to investigate preoperatively TEG-Hypercoagulable CABG patients. The rationale being that this is a patient population with a heightened thromboembolic risk (including graft occlusion) due to the hypercoagulability, but, hence, also is at low risk for bleeding on dual antiplatelet therapy. We hypothesize that this subgroup of CABG patients will benefit the most on a dual antiplatelet regimen both in regards to SVG patency and thromboembolic complications in general.

Examining hemostatic ability and status before and after surgery/intervention with TEG, we believe will be the future for postoperative thromboembolic risk evaluation. Including Multiplate aggregometry measurements in our trial will also help elucidate if resistance measurements after cardiac surgery can help better tailor antiplatelet regimens. These points become even more important as the patients referred to cardiac surgery get older and have more co-morbidities, and, hence, have limited physiological reserves, where graft occlusions and even small thromboembolic episodes can have detrimental effects on overall health and survival.

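### Table 1 prints the platelet-count exclusion, and secondarily the infarction exclusion, in a direction that conflicts with the neighbouring criteria and the trial's stated rationale

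*Protocol article*

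**What the plan says.** Table 1 of the protocol article gives the criteria for entry. Two exclusions are at issue: "Platelet count >150 E9" and "Myocardial infarction >48 h of surgery".

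The same list also excludes ongoing bleeding, known platelet disease and prior peptic ulcer. Its other timed entries are "Cardiac Shock within 48 h of surgery", "Prior CABG surgery within one month" and a cerebral event (ICH/TCI) in the preceding 30 days. The Study population section restricts the trial to isolated, non-emergent CABG, and the inclusion criteria describe the surgery as elective or subacute.

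The Discussion justifies the choice of population by saying that it has a raised thromboembolic risk but "also is at low risk for bleeding on dual antiplatelet therapy".

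On the TEG threshold, the Abstract says "TEG-Hypercoagulability is defined as a TEG maximum amplitude above 69 mm", and the section on design and randomisation uses the same strict cut-off. The section describing the TEG assay says "MA values above or equal to 69 mm are diagnosed TEG-Hypercoagulable" and attributes this to the manufacturer.

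**The concern.** These two lines decide who may be randomised; they are not background. A site or reader following the platelet line literally would turn away every patient with a count above 150 E9 and keep only those at or below it. The intervention is dual antiplatelet therapy. The Background acknowledges that this raised bleeding risk in other coronary populations, and the section on the medical intervention says that a larger loading dose was avoided because of bleeding concerns. An entry rule that keeps only the lower counts sits badly with that reasoning.

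The infarction line has a similar problem of direction. Read literally, it removes patients whose infarction lies more than 48 hours from surgery, with no outer limit, and leaves those within 48 hours eligible.

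At stake are the population to which the result applies and the consistency of the entry rules with the trial's own safety reasoning. Enrolment was continuing when the article appeared.

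**Working it through.** No calculation decides this point. The check is to set the entries side by side.

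**Platelet line**

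| Entry or statement (location) | Who is removed or described |
|---|---|
| Platelet line, as printed (Table 1) | counts above 150 E9 removed; at or below 150 E9 kept |
| Ongoing bleeding (Table 1) | patients at raised bleeding risk removed |
| Known platelet disease (Table 1) | patients with abnormal platelets removed |
| Prior peptic ulcer (Table 1) | patients at raised bleeding risk removed |
| Rationale (Discussion) | target population described as having low bleeding risk |
| Meaning of TEG hypercoagulability (Background) | high platelet-fibrin clot strength |

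The three neighbouring entries remove patients in whom bleeding is more likely. The platelet line, as printed, removes the higher counts. It is the only entry in this group that runs that way, and the article offers no reason for it.

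**Infarction line**

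| Timed exclusion in Table 1 | Which events are removed |
|---|---|
| Cardiac shock, 48 hours | recent |
| Prior CABG, one month | recent |
| ICH/TCI, 30 days | recent |
| Infarction, 48 hours, as printed | older; recent ones admitted |

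Three of the four timed entries remove recent events, and the infarction line alone does the reverse. Admitting an infarction within 48 hours while barring older ones also fits poorly with a population limited to non-emergent, elective or subacute surgery.

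**Is the symbol merely a damaged character?** This is unlikely. A less-than sign appears intact in a P value in the Background, and the other greater-than signs in Table 1 (age, liver enzymes, creatinine) read sensibly. A slip when the article was written or typeset remains possible.

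**How many patients are affected?** Let q be the share of otherwise eligible candidates with a count above 150 E9. The printed rule removes exactly the share q. The article gives no value for q, so it could lie anywhere from 0 to 1. The infarction line has the same gap, because no timing distribution is given.

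**Does the sample size depend on these lines?** It does not. The inputs in the Sample size section are 80% and 90% patency, 80% power and a 5% level (taken as two-sided, which the article does not state).

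- Uncorrected: n = [1.96 × √(2 × 0.85 × 0.15) + 0.8416 × √(0.8 × 0.2 + 0.9 × 0.1)]² / 0.10² = 198.97, rounded up to 199.
- With continuity correction: (198.97/4) × [1 + √(1 + 4/(198.97 × 0.10))]² = 218.5, rounded up to 219 grafts per group, as the article states.

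Neither entry threshold enters this calculation.

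**TEG cut-off.** The Abstract and the randomisation section both use above 69 mm, and the Background uses the same for the group's earlier cohort. Only the assay section includes 69 mm itself. The difference concerns only patients at exactly 69 mm, and the article does not say how many there are.

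**The case against.** The best defence is that these are sign slips in a published table. On that view nobody chose to exclude higher platelet counts, no endpoint, analysis, error rate or sample size is affected, and an erratum is enough. Much of this stands: the entries around the two lines do point to a reporting error more than a deliberate design. But the article presents the table as the trial's entry criteria, and it cannot show whether the same wording reached the working documents. A short check of records is therefore reasonable as well as an erratum.

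A second objection is that the Discussion ties low bleeding risk to hypercoagulability and does not mention platelet count, so the conflict with the rationale is inferred. That is fair. The neighbouring exclusions are the firmer evidence for the platelet line. The infarction line rests mainly on its inconsistency with the other timed entries, and its wording is awkward enough that the literal reading is itself an interpretation.

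Some stronger readings are tempting but not supported:

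- A reader might infer that the printed rule shuts out nearly everyone the trial targets. That needs a platelet-count distribution, which the article does not give.
- A reader might infer that the wrong patients were in fact randomised. The article does not show which rules were applied.
- A reader might set the infarction line against the Perioperative anticoagulation section ("In patients with acute coronary syndrome 40 mg of Clexane"). That section says nothing about infarction timing. Acute coronary syndrome without infarction, or with one inside 48 hours, remains eligible under the printed line, so there is no contradiction.
- A reader might say that the entry thresholds contradict one another or leave the trial population undefined. The platelet, infarction and TEG items are separate matters. The TEG entry rule is identifiable from the randomisation section, since the inclusive version is credited to the manufacturer.

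**Conclusion.** The point holds in this form. As printed, the platelet exclusion admits only counts at or below 150 E9, which is inconsistent with the adjacent bleeding-risk exclusions and, by inference, with the low-bleeding-risk rationale. Secondarily, the infarction exclusion runs opposite to the other three timed exclusions and fits poorly with a non-emergent population. Both lines need correction or explanation because they govern who may be randomised.

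The conclusion rests on reading the two lines literally and assumes nothing about the distribution of patients. The number of patients affected, and whether any were enrolled under the printed rules, cannot be determined from the article. The planned 219 grafts per group is unaffected. The TEG wording is a minor editorial matter and adds nothing to the weight of the main point. No view is taken here on which platelet or infarction threshold is clinically right.

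**What to change.** 1. Compare the direction of the platelet and infarction exclusions with the ethics-approved protocol, and correct Table 1 to the rules actually applied. If the printed direction was intended, state the reason.
2. Confirm from the existing screening records that the 135 patients already randomised, and those enrolled since, met the approved criteria. Report any who did not.
3. In the TEG assay section, either bring the 69 mm wording into line with the cut-off in the Abstract and the randomisation section, or mark it as the manufacturer's definition only.

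The cost is a correction to two lines of a table and one sentence, plus a check of records already held. No new data, change of sample size or change of analysis is needed to make the correction. If the check finds patients enrolled outside the approved criteria, their handling would need a separate decision.
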